## Abstract

**Background:**

Depression and anxiety disorders during adolescence can have detrimental consequences. Both disorders are related to negative outcome in various areas during adolescence and are also predictive of depression and anxiety disorders later in life. Especially parental psychopathology and being female are risk factors that increase the probability of developing one of these disorders during adolescence. Research has shown that prevention programs have promising results, especially for adolescents who have these risk factors. Therefore, in this study, we will focus on the effectiveness of a prevention program ‘A jump forward’ that has been developed for adolescent girls with a familial risk of depression and/or anxiety.

**Methods/Design:**

We designed a randomized controlled trial to test the effectiveness of an indicated and selective prevention program aimed at depression and anxiety in adolescent girls. Adolescents aged between 11 and 15 years old with depressive and/or anxiety symptoms and with parents who show indicators of parental psychopathology will be randomly assigned to the experimental (N = 80) or control groups (N = 80). Participants in the experimental group will follow a preventive intervention, consisting of six sessions of 90 minutes each. All participants will complete baseline, intervention phase 1 (after session 2), intervention phase 2 (after session 4), post-intervention, 6 month follow-up, and 12 month follow-up assessments. Furthermore, parents will be asked to complete assessments at baseline, post-intervention, and 12-month follow-up. Primary outcome will be depressive symptoms. Secondary outcomes will be anxiety symptoms, suicidal ideation, response style, negative cognitive errors, parental emotional support and parental control, parental psychopathology, parenting stress and adolescents’ depression and anxiety symptoms according to the parents.

**Discussion:**

This paper described the study designed to evaluate a program for preventing depression and/or anxiety in high-risk adolescents over a 12-month follow-up period. If the program showed to be effective in reducing symptoms of depression and anxiety and preventing adolescents from developing clinical levels of these disorders, our results would be relevant to practice. Thus, the intervention could be used on a large scale. Moreover, this study aims to contribute to the evidence-based prevention of depression and anxiety of adolescents.

**Trial registration:**

Dutch Trial Register NTR3720

## Background

Depression and anxiety disorders are a major public health concern. The prevalence of clinical depression in adolescents is approximately 5.6% [1]. Regarding anxiety disorders, prevalence rates in children and adolescents vary from 3% to 20% [2]. In addition, lifetime prevalence of depression in adolescents is suggested to be 28.8% and of anxiety disorders, lifetime prevalence is estimated at 16.6% [3]. These numbers do not even include children and adolescents with increased levels of depressive and anxiety symptoms, which are just below the diagnostic threshold [3].

Depression and anxiety disorders during adolescence can have detrimental consequences. That is, both disorders at this age are related to negative outcomes in various areas, such as poor psychosocial functioning [4], impairment in social relations [5], poor academic performance [4,5], and an increased risk for substance abuse [4]. Furthermore, adolescent depression and anxiety are both associated with depression, anxiety disorders, and even suicide later in life [6,7]. Not only clinical levels of depression or anxiety have negative outcomes, also subclinical levels of depression or anxiety are associated with significant distress and dysfunction, and they are also a risk for future disorders [7-9].

It is important to examine the role of risk factors to understand the onset and maintenance of psychopathology during adolescence. With respect to depression and anxiety disorders, several factors increase the probability of developing one of these disorders. The first important risk factor is parental psychopathology, as children of parents with a depression are three times more likely to develop an episode of a major depressive disorder compared to children whose parents do not have this disorder [4,10,11]. With regard to anxiety, 68% of children of parents with this disorder show symptoms of an actual anxiety disorder [12]. Furthermore, these children are two to seven times more likely to develop an anxiety disorder compared to children of parents without an anxiety disorder [13-17]. Moreover, children of parents with an anxiety disorder, a depression, or both, have significantly higher odds of developing depression or anxiety compared to children of parents without these disorders [16]. The first explanation is that these children experience more stress at home and that their parents have less parenting skills. Nevertheless, the relations between particular patterns of depression and anxiety symptoms in adolescents on the one hand and parental psychopathology, parenting characteristics, parental emotional support, and parental control on the other hand remain to be further specified. The second explanation is that a genetic predisposition increases the probability of developing mood and anxiety disorders. Theorists assume that depression and anxiety disorders are familial disorders and partly the result of a genetic heredity. However, the largest part of evidence suggests that depressive and anxiety symptoms rather than specific disorders are heritable. This genetic influence accounts for 30-50% of the variance in these symptoms [18-23]. The second risk factor in the development of depression and anxiety during adolescence is gender. Females have been identified as being at a higher risk of developing depression and anxiety disorders [24-26]. Differences between boys and girls seem to arise during puberty, and particularly adolescent girls are vulnerable to develop a clinical depression [27] and often show subclinical depressive and anxiety symptoms [28].

Given the high prevalence rates of depression and anxiety disorders in children and adolescents as well as the effect these disorders have on their current and future psychosocial functioning, many treatment programs have been developed. Most of these programs are based on cognitive behavioral therapy (CBT), which addresses, for example, dysfunctional emotions, maladaptive behaviors, and cognitive processes. That is, these negative cognitions generally result in higher levels of depression and anxiety. This implies that response style and cognitive errors are assumed to mediate the relation between prevention programs and symptoms of depression and anxiety. CBT is known to be effective in treating and preventing depression and anxiety in adolescents [29-31] individually as well as in groups [32,33]. Importantly, it has been shown that the coping skills learned from a CBT intervention could mediate the relation between family stressors and the actual development of adolescent depression or anxiety disorders [34].

Adolescents with symptoms of depression and/or anxiety who have parents with elevated levels of depression and/or anxiety have a relative high risk to develop depression or anxiety disorders later in life. Because children of parents with a mental illness often develop maladaptive self-schemas as a consequence of negative family-related events, CBT would be a preferred intervention [34]. Despite these facts, to date, only a limited number of studies have been conducted to examine the prevention of depression and/or anxiety disorders in adolescent offspring of depressed or anxious parents by means of CBT [35-38]. The findings showed that preventive interventions had positive outcomes, such as decreased symptomatology. However, none of these preventive interventions targeted both depression and anxiety, although these disorders have a high comorbidity, simultaneous development [39,40], and a considerable overlap in symptoms, especially during adolescence [41]. Since the aetiology and pathogenesis of depression and anxiety also overlap substantially, we argue that the prevention programs should focus on both disorders simultaneously, specifically during adolescence. Therefore, common factors can be prevented, and there might be greater potential to obtain benefits [42,43].

The current study combines indicated prevention and selective prevention [44], which respectively refer to the prevention provided to adolescents with elevated levels of depression or anxiety and to the prevention provided to targeted subgroups distinguished by specific traits, in our case children who have parents with elevated levels of depression or anxiety. As mentioned above, these adolescents have an extra high risk to develop a depression or anxiety disorder. The adolescents allocated to the experimental group will undergo a preventive intervention that consists of six weekly meetings of 90 minutes each. It will focus on acquiring knowledge of depression and anxiety, learning to recognize and distinguish emotions, dealing with difficult situations, solving social problems, and creating and using a supportive social network. Throughout the program, the adolescents will complete various exercises based on cognitive behavioral therapy, behavioral activation, and exposure.

The primary aim of this study is to test the effectiveness of the program ‘Een Sprong Vooruit’ [A Jump Forward] in preventing depressive and anxiety symptoms among adolescents with elevated symptoms of depression and anxiety who have parents with elevated symptoms of depression and/or anxiety. The secondary aim is to determine whether response style and cognitive errors mediate and whether parental psychopathology, parenting stress, parental emotional support and parental control moderate the effectiveness of the prevention program.

## Methods

The study design will be reported in accordance with the CONSORT 2010 statement for reporting parallel group randomized trials [45]. The medical ethics committee CMO Region Arnhem-Nijmegen, The Netherlands, has approved this study.

### Design

The present study is designed as a non-blinded randomized controlled trial (RCT) with two conditions (intervention versus control). Adolescents will be screened for depression, anxiety, suicide ideation, and parental psychopathology in order to select high-risk adolescents. The program is designed for indicated and selective prevention [44]; therefore, adolescents with elevated symptoms of depression and/or anxiety as well as with a parent who has elevated levels of depression or anxiety symptoms will be selected and recruited.

After the completion of screening and recruitment, participants will be randomized to either intervention or control group. The assessments will be conducted at baseline (T0), during the intervention phase after session 2 (T1), during the intervention phase after session 4 (T2), at post-intervention (T3), at 6-month months follow-up (T4), and at 12-month follow-up (T5). The overall study design is captured in Figure 1.

**Figure 1 F1:**
[figure not shown]
Overall study design.

### Participants’ eligibility

Adolescents with depressive and/or anxiety symptoms who are willing to participate in a prevention program will be eligible for this study. Inclusion criteria are age between 11-15 years old; increased levels of depression and/or anxiety; at least one of the parents showing symptoms of a depression or anxiety disorder; and both adolescent and parents having sufficient knowledge of the Dutch language. Exclusion criteria are the absence of parental permission; adolescent already receiving treatment for mental health problems; and presence of prominent suicidal ideation (score 2 on CDI item: a desire to kill oneself, if given the chance).

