### Sample size

The sample size is based on the expected difference (Cohen’s d = 0.50) on the primary outcome variable between the experimental and control group at 12 months follow-up (based on a meta-analytic review [46]). With an alpha of 0.05 and a power of 0.80 of a two-tailed test, 64 participants will need to be included in each condition. The data will be analyzed according to the intent-to-treat principle. Multiple imputations will be used for missing observations at follow-ups. We intend to increase the sample size by 25% to compensate for dropout and potential loss of power due to clustering of data, resulting in 160 participants (80 in experimental condition and 80 in control condition).

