### Primary outcome measure

*Depression* in children and adolescents will be measured with the CDI 2 [47]. The CDI 2 contains 28 items, each consisting of three statements graded in severity from 0 to 2. This instrument has good internal consistency and convergent validity [48].

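### Girls can enter on anxiety alone, but the only primary outcome is depression, and d = 0.50 is applied to the whole mixed sample without allowance or justification

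*Protocol article*

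**What the plan says.** The Participants' eligibility section of the protocol article requires "increased levels of depression and/or anxiety". The Design section agrees: the trial selects "adolescents with elevated symptoms of depression and/or anxiety as well as with a parent who has elevated levels of depression or anxiety symptoms". Neither section sets a minimum depression score, so a girl with raised anxiety and unremarkable depressive symptoms qualifies.

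The abstract states "Primary outcome will be depressive symptoms", and the Primary outcome measure section names the CDI 2 as the instrument. Anxiety is placed lower: "Secondary outcomes will be anxiety symptoms, suicidal ideation, response style, negative cognitive errors".

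The Sample size section rests on the "expected difference (Cohen’s d = 0.50) on the primary outcome variable between the experimental and control group at 12 months follow-up". It credits this value to a meta-analytic review and does not describe the populations in it. It then adds 25% for dropout and clustering.

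The primary aim, at the end of the Background section, describes a different population. The programme is to be tested "among adolescents with elevated symptoms of depression and anxiety who have parents with elevated symptoms of depression and/or anxiety". For the girls the conjunction is 'and'; for the parents it is 'and/or'.

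The Data analysis section says that baseline differences in demographics, depressive symptoms and anxiety symptoms will be checked. Variables whose distributions differ between arms are then to be entered as confounders in the effectiveness models.

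**The concern.** Three elements fixed in this article do not clearly fit together: who may enter, what is tested as primary, and the effect size assumed for that test. For a girl who qualified on anxiety, relief of the symptom that qualified her does not count towards the primary test. Her contribution depends on a depression effect that the plan assumes to be as large as everyone else's, without giving a reason.

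If that assumption fails for a sizeable subgroup, the average effect falls below 0.50 and so does power. A null CDI 2 result would then be harder to read, because it could reflect an ineffective programme or a sample in which part had less scope to change on the primary outcome. Separately, the aim taken literally describes a narrower population than the one enrolled, so readers could differ about whom the result applies to.

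**Working it through.** **Reproducing the plan's figure.** Inputs from the Sample size section: d = 0.50, two-sided alpha 0.05, power 0.80. The two-sample t-test needs 63.77 per arm, rounded up to 64 (the normal approximation gives 63). Then 64 × 1.25 = 80 per arm, 160 in total. Since 80 × (1 − 0.20) = 64, the margin covers a combined 20% loss from dropout and clustering and leaves nothing for a mixed-entry sample. The arithmetic is correct.

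**Assumed inputs (not in the documents).** Let q be the share entering on anxiety alone and d_a their CDI 2 effect. Both are unknown. I take q = 10%, 20% and 30%, with d_a = 0 (worst case) or d_a = 0.25 (half of 0.50).

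**Formula.** Average effect: d = (1 − q) × 0.50 + q × d_a. Power comes from the noncentral t distribution with 2n − 2 degrees of freedom and noncentrality d × √(n/2). The SD is held at 1.

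Example with q = 20% and d_a = 0: d = 0.80 × 0.50 = 0.40. With n = 64 the noncentrality is 0.40 × √32 = 2.26, against 0.50 × √32 = 2.83 without dilution. Power falls from 0.801 to 0.612.

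| Share q | d if d_a = 0 | Power, 64 per arm | Power, 80 per arm | d if d_a = 0.25 | Power, 64 per arm | Power, 80 per arm |
|---|---|---|---|---|---|---|
| 0% | 0.50 | 0.801 | 0.882 | 0.50 | 0.801 | 0.882 |
| 10% | 0.45 | 0.714 | 0.808 | 0.475 | 0.760 | 0.848 |
| 20% | 0.40 | 0.612 | 0.710 | 0.45 | 0.714 | 0.808 |
| 30% | 0.35 | 0.502 | 0.595 | 0.425 | 0.665 | 0.762 |

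The columns for 80 per arm assume no dropout and no clustering loss, which the plan itself does not expect. In that best case, and with no effect in the subgroup, power stays at 0.80 up to q of about 11% (d = 0.89 × 0.50 = 0.445). With half the effect kept, the same d is reached at twice that share, about 22%. At 64 analysable per arm there is no slack.

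**Limit of the calculation.** If the two entry groups differed by one SD in mean CDI 2, the pooled SD would rise from 1 to √(1 + 0.2 × 0.8) = 1.08 at q = 20%, which would lower power a little further. Adjusting for baseline CDI 2 would work against this.

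**The case against.** The strongest reply is that no dilution has been demonstrated. The Background section reports high comorbidity, simultaneous development and overlapping symptoms in adolescence, and gives these as the reason for a combined programme. The anxiety-only share may therefore be small, and such girls may still carry depressive symptoms. This stands: both q and d_a are assumptions.

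A reader might infer that these girls start near the bottom of the CDI 2, or that they can benefit only if comparable controls become depressed. The article supports neither. It gives no cut-off and no CDI 2 values, and missing a depression criterion is not the same as scoring at the floor. The CDI 2 is a symptom score, so smaller worsening than in controls counts as benefit. That is what a prevention trial looks for.

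A reader might also infer that 0.50 comes from samples selected for depression. The population behind the cited review is not described. If it already includes mixed samples, discounting by q would count the dilution twice.

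On imbalance, the Data analysis section does check depressive and anxiety symptoms at baseline and adjusts for variables that differ. That answers part of the worry, but only conditionally: the covariate set of the primary model is not known until the data have been inspected. Nor is it true that a null result could never be explored, since CDI 2 and SCAS are collected at screening and at every adolescent assessment. What is lacking is a commitment made beforehand.

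Finally, stratification factors and subgroup estimates are often left to a fuller document, so their absence is not itself an error. They appear below only as remedies.

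**Conclusion.** The mismatch holds. Entry is on depression and/or anxiety, the primary test is on depression alone, and d = 0.50 is applied to all entrants with a margin reserved for other losses. The stated power of 0.80 is therefore conditional on 0.50 being the average effect in the and/or sample as a whole, which the article neither states nor justifies.

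The size of the problem cannot be fixed from the document. Over assumed shares of 10% to 30%, power with 64 per arm runs from 0.71 down to 0.50 if the subgroup has no CDI 2 effect, and from 0.76 down to 0.67 if it keeps half. With all 80 per arm retained, the no-effect case runs from 0.81 to 0.60.

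It would go too far to conclude that the trial is underpowered or that its sample size calculation is wrong. The first depends on an unknown share and effect; the second is contradicted by the reproduced figure. The 'and' in the primary aim conflicts with the Design and eligibility sections. It looks like a wording slip, but it concerns the target population and should be reconciled.

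**What to change.** Eligibility and sample size stay as they are.

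1. In the Data analysis section, replace the rule of adjusting only for variables found to differ, as far as the primary model is concerned, with a fixed adjustment for baseline (or screening) CDI 2. If feasible, also stratify randomisation by whether the depression criterion was met at screening. CDI 2 and SCAS are already administered then, before randomisation, so no new data are needed.
2. Prespecify two supportive estimates beside the all-participant result: the CDI 2 effect in girls who met the depression criterion, and the SCAS effect in girls who met the anxiety criterion.
3. Align the population in the primary aim with the 'and/or' of the Design and eligibility sections. Add to the Sample size section that power of 0.80 holds only if d = 0.50 applies to the and/or sample as a whole.

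The cost is one covariate, possibly one stratification factor, two supportive estimates and some wording. The downside is limited precision in the subgroup estimates, which should not be read as confirmatory, and a more guarded power statement.

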### Recruitment

Students in their first and second year of secondary school, from vocational training up to pre-university level, will receive written information about the screening and the study. After receiving passive consent, these students will be screened for depression, anxiety, and parental psychopathology. Students who meet the inclusion criteria will be randomly assigned to one of the two conditions. After that, the adolescents and their parents will receive verbal and written information about the study and written informed consent from adolescents and parents will be obtained.

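### The Recruitment section places randomisation before the families' study information and written consent, which contradicts the Design section and lets permission and willingness act as post-randomisation filters

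*Protocol article*

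**What the plan says.** The Recruitment section of the Protocol article gives this sequence:

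1. Students "will receive written information about the screening and the study".
2. "After receiving passive consent, these students will be screened for depression, anxiety, and parental psychopathology".
3. "Students who meet the inclusion criteria will be randomly assigned to one of the two conditions".
4. "After that, the adolescents and their parents will receive verbal and written information about the study and written informed consent from adolescents and parents" are obtained.

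The Design section gives another order: "After the completion of screening and recruitment, participants will be randomized to either intervention or control group". It also describes the trial as non-blinded.

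The eligibility section restricts entry to adolescents "who are willing to participate in a prevention program will be eligible for this study" and adds: "Exclusion criteria are the absence of parental permission", followed by two further exclusions.

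On analysis, the Sample size section states: "The data will be analyzed according to the intent-to-treat principle". Multiple imputation is planned for observations missing at the follow-ups. The 25% increase from 64 to 80 per arm is attributed to dropout and clustering. The Discussion makes clear that control adolescents get no prevention programme.

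**The concern.** Recruitment ordinarily includes consent, and the article's own Recruitment section contains the consent step. On that meaning, the Design and Recruitment sections cannot both be followed.

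If the Recruitment order is the one used, two eligibility criteria are settled only after the arm is fixed. One arm means six 90-minute sessions; the other means assessments without a programme. A family that knows which it has been given may decide differently about joining. The adolescents who go on to be analysed would then be selected by arm, and the two groups would no longer be the groups that randomisation formed.

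The planned analysis does not reliably repair this. Imputation is described for missing follow-ups, whereas a student who refuses written consent would presumably contribute nothing from T0 onwards. The article does not say how such students are counted under intention-to-treat. The rule that variables found to differ between groups are entered as confounders can deal only with differences that were measured.

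**Working it through.** **Order of steps**

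| Step | Recruitment section | Design section |
|---|---|---|
| Initial written information, passive consent | before screening | not mentioned |
| Screening | before randomisation | before randomisation |
| Verbal and written information, written consent | after randomisation | before randomisation, if recruitment includes consent |

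The conflict concerns the last row. The willingness and permission criteria depend on that row, unless permission means only the passive consent to screening.

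**The plan's own sample size.** Inputs from the Sample size section: d = 0.50, two-sided alpha 0.05, power 0.80. The two-sample t-test requires 63.77, so 64 per arm, as stated. Then 64 x 1.25 = 80 per arm, or 160 in total. Power is 0.80 at 64 per arm and 0.88 at 80.

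**Possible bias if the arm is known at consent.** The article gives no consent rates, so everything here is assumed. Let pc and pi be the proportions consenting in control and intervention, with pi below pc, and suppose that everyone who would consent under intervention would also consent under control. Let D be the difference in 12-month CDI 2, in SD, between those who consent only under control and those who consent under either arm. The control group then contains a fraction (pc - pi)/pc of the extra consenters, so:

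bias = (pc - pi) x D / pc

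With pc = 0.90:

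| pi | D = 0.25 | D = 0.50 | D = 0.75 |
|---|---|---|---|
| 0.80 | 0.10 x 0.25/0.90 = 0.03 | 0.06 | 0.08 |
| 0.70 | 0.06 | 0.20 x 0.50/0.90 = 0.11 | 0.17 |
| 0.60 | 0.08 | 0.17 | 0.30 x 0.75/0.90 = 0.25 |

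The central cell, 0.11 SD, is 22% of the planned 0.50. As a simpler check, suppose all control families consent and 20% to 30% refuse in intervention, with D = 0.50. The shift is 0.20 x 0.50 = 0.10 to 0.30 x 0.50 = 0.15 SD. The sign of D is not known. If control families refused more often instead, the bias would run the other way for the same sign of D.

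**Possible loss of numbers if the 160 are counted at randomisation.** Refusal rates are assumed and equal in both arms; power is at d = 0.50, before other dropout or clustering.

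| Refusal | Left per arm | Power | Randomise per arm to keep 80 |
|---|---|---|---|
| 10% | 72 | 0.85 | 89 |
| 20% | 64 | 0.80 | 100 |
| 30% | 56 | 0.75 | 115 |
| 40% | 48 | 0.68 | 134 |

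At 20%, 80 x 0.80 = 64, so the whole allowance is gone before any dropout or clustering.

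**What is measured before allocation.** Table 1 and the Screening measures section place the CDI 2 and SCAS at screening, which precedes randomisation in both orders. The parent-completed BSI and OBVL are first taken at T0; the BSI is taken only then. Both feed planned moderators. The article does not state when T0 falls relative to allocation.

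**The case against.** The strongest reply is that the Recruitment sentence may be loose drafting in a condensed article. The Design section has the conventional order, and making willingness a condition of eligibility fits it. Parental permission might mean the passive consent to screening. Figure 1 could not be seen for this review and may show the order. All of this is possible, but it would not remove the conflict between two explicit sentences, and a reader cannot tell which order applies.

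Four stronger readings are tempting and are not supported:

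- *That students are randomised uninformed.* The Recruitment section gives them written information on the screening and the study at the outset. What follows assignment is the further verbal and written information to adolescents and parents, and the written consent.
- *That consent depends on arm.* Fixed allocation is not disclosed allocation. The article nowhere says that families learn their arm before signing. If the arm stayed hidden until then, refusal could not depend on it. The article merely fails to prevent early disclosure.
- *That the baseline is contaminated.* The timing of T0 is not stated, and the screening CDI 2 and SCAS are safe pre-allocation covariates. If refusers' screening data may be used, they would also allow a check for differential refusal. They would not remove bias from unmeasured differences.
- *That refusals will erode the 160.* The Sample size section may equally mean enrolled, consented participants.

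These replies limit the claims about consequences. They leave the contradiction in place.

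**Conclusion.** The point holds as a contradiction on the timing of written consent, with high confidence. Followed literally, the Recruitment section lets the willingness and permission criteria operate after randomisation in a non-blinded trial.

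The consequences are conditional. Bias requires that allocation is known before consent, that refusal then differs by arm, and that the adolescents gained or lost differ in outcome. Its direction and size cannot be determined from the article; the range of 0.03 to 0.25 SD only illustrates the assumed rates. The loss of power requires, separately, that the 160 are counted at randomisation.

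It should be corrected despite this uncertainty, because selection after allocation threatens the comparison itself, cannot be reliably undone in the analysis, and is cheap to rule out in advance.

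**What to change.** Rewrite the Recruitment section, and align the Design section with it, so that both give one order: screening; verbal and written study information; written consent from adolescent and parents; T0; randomisation; disclosure of allocation. State that the 160 are participants who have given written consent.

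The cost is a wording change or small amendment, plus a short wait between T0 and allocation. No additional participants are needed.
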